## Abstract

**Background:**

Unintended pregnancy can negatively impact women’s lives and is associated with poorer health outcomes for women and children. Many women, particularly in low- and middle-income countries, continue to face obstacles in avoiding unintended pregnancy. In the State of Palestine, a survey conducted in 2006 estimated that 38% of pregnancies are unintended. In 2014, unmet need for contraception was highest among young women aged 20–24 years, at 15%.

Mobile phones are increasingly being used to deliver health support. Once developed, interventions delivered by mobile phone are often cheaper to deliver than face-to-face support. The London School of Hygiene and Tropical Medicine and the Palestinian Family Planning and Protection Association have partnered to develop and evaluate a contraceptive behavioural intervention for young women in Palestine delivered by mobile phone. The intervention was developed guided by behavioural science and consists of short, mobile phone text messages that contain information about contraception and behaviour change methods delivered over 4 months.

**Methods:**

We will evaluate the intervention by conducting a randomised controlled trial. Five hundred and seventy women aged 18–24 years, who do not report using an effective method of contraception, will be allocated with a 1:1 ratio to receive the intervention text messages or control text messages about trial participation. The primary outcome is self-reported acceptability of at least one method of effective contraception at 4 months. Secondary outcomes include the use of effective contraception, acceptability of individual methods, discontinuation, service uptake, unintended pregnancy and abortion. Process outcomes include knowledge, perceived norms, personal agency and intervention dose received. Outcomes at 4 months will be compared between arms using logistic regression.

**Discussion:**

This trial will determine the effect of the intervention on young women’s attitudes towards the most effective methods of contraception. If the intervention is found to be effective, the intervention will be implemented widely across Palestine. The results could also be used to design a larger trial to establish its effect on unintended pregnancy.

**Trial registration:**

ClinicalTrials.gov, ID: NCT02905461. Registered on 14 September 2016.

**Electronic supplementary material:**

The online version of this article (doi:10.1186/s13063-017-2191-1) contains supplementary material, which is available to authorized users.

## Background

In 2012, an estimated 85 million pregnancies worldwide were unintended, half of which ended in abortion [1]. Women who have unintended pregnancies can experience decreased psychological wellbeing [2–10], initiate antenatal care later than those with intended pregnancies [4, 10–14] and access care less frequently [4, 11, 14]. There is a higher risk of low birth weight and pre-term birth among children born of unintended pregnancies [15, 16] and these children can exhibit behavioural problems more often than children born of intended pregnancies [17]. Unintended pregnancy can also impact the social wellbeing of parents and families. It can delay or prevent educational and career achievements, which can impact the financial security of the family [18]. Unsafe abortions are a consequence of unintended pregnancy where access to safe abortion is limited [19, 20]. Satisfying unmet need for modern contraception reduces unintended pregnancies and identifying the barriers to non-use is crucial in achieving this [21, 22].

The conflict in the State of Palestine (the West Bank, East Jerusalem and the Gaza Strip, hereafter referred to as ‘Palestine’) has negatively impacted the health and wellbeing of Palestinians [23–25]. The conflict has also had negative effects on reproductive health in Palestine [26, 27]. Data regarding unintended pregnancy in Palestine generally comes from household surveys where only married women (sexual activity before marriage is stigmatised in Palestinian culture) are asked if their current or last pregnancy was intended at the time that they became pregnant [28]. Effective contraception methods are those with a less than 10% typical use-failure rate at 12 months [29–31]. The (non-permanent) effective methods available in Palestine are oral contraceptive pills (OCs), intrauterine devices (IUDs), injectables, implants, and the patch. Despite the availability of these methods, a 2006 survey estimated that 38% of pregnancies in Palestine are unintended [28, 32].

In 2014, the unmet need for contraception was highest among young women aged 20–24 years, at 15% [33]. The modern contraceptive prevalence rate among married women aged 15–24 years is estimated to be 24% and the effective rate in the same group is estimated to be 17% [33]. Barriers to contraceptive uptake are lack of accurate and comprehensive information about a range of contraceptive methods, lack of spousal communication regarding contraception, peers’ and relatives’ (particularly husband and mother-in-law) disapproval of contraception, societal pressure to bear children early in marriage and inadequate family planning services [34–38]. Attitudes, such as perceived inconvenience and fear of the side effects of contraceptive methods along with husbands’ opposition, are common reasons married women provide for not using contraception [39, 40]. Education also is a factor in this setting as Palestinian women who spend more time in education report fewer unintended pregnancies [28]. A non-representative study in 2014 and found that 55% of women aged 15–49 years from a community sample (from underserved areas) said that their pregnancy was unintended (‘unwanted’) and, of these, 26% said that this was because it ‘was not their choice’. In a client sample (from service-delivery points), 40% reported unintended pregnancy, with 32% saying that it ‘was not their choice’ [41].

Mobile phones are increasingly being used to deliver health support over a range of health behaviours [42–52]. In sensitive areas, such as reproductive and sexual health, short messages delivered by mobile phone may be advantageous as they have the potential to be read at a time and place of the recipient’s choosing. The support can be non-judgemental and is often more convenient and cheaper to deliver than face-to-face support. In Palestine, where there is a substantial area that is underserved with regard to sexual and reproductive health services [41], delivering contraceptive support by mobile phone may be a particularly advantageous mode by which to reach people. Those that do have access to services may find the barriers outlined above difficult to overcome and may also benefit from mobile phone support. While there is some evidence from high-income countries that mobile phone-based interventions can increase contraceptive-related behaviours [53–55] and knowledge [56], none of the trials evaluating these interventions had a low risk of bias [57]. To the best of our knowledge, there is only one trial conducted in a non-high-income country (Cambodia); this trial found that post-abortion voice messaging with telephone counselling support increased effective contraceptive use [58].

A systematic approach to developing behaviour change interventions is recommended [59–61] as it allows for the intervention to be clearly defined. The London School of Hygiene and Tropical Medicine (LSHTM) and the Palestinian Family Planning and Protection Association (PFPPA), a Member Association of the International Planned Parenthood Federation (IPPF), are collaborating to evaluate a contraceptive behavioural intervention delivered by mobile phone for young women in Palestine. We developed the intervention guided by an established approach based on behavioural science [62]. Among other activities, the approach involved consultation with young people, which explored their knowledge of, attitudes towards, and barriers in, using contraception; specifying behavioural change; identifying behaviour change methods and producing the intervention content through an interactive process of writing, testing with young people and refining.

In Palestine, mobile phone ownership is high, with 92% of all adults owning a mobile phone and among people aged 18–34 years, 73% report owning a smartphone [63]. However, the intervention development process revealed that many young people in Palestine did not have regular Internet access on their mobile phones. Those who sometimes access the Internet though their mobile data said that it is common for the connection to be lost. Because of this and because many of the young people we consulted with preferred it, we identified short messaging service (SMS) as the most appropriate mode of intervention delivery.

This randomised controlled trial will evaluate the effect of the intervention on young women’s attitudes towards the (non-permanent) effective contraceptive methods available in Palestine: OCs, IUDs, the injection, the implant, and the patch. Sexual activity before marriage is highly stigmatised in Palestine and there is strong cultural pressure to bear children soon after marriage. While it is estimated that 24% of women are married before age 18 years [33], a significant proportion of participants in the study population will likely be either not married (and not sexually active or not willing to admit that they are) or newly married. Because of this, an objective primary outcome of effective contraceptive use would not be advisable as powering a study for an outcome with a small number of events would make the sample size prohibitively large. In not-married/not-sexually-active young women, the intervention aims to increase acceptability of the effective methods for when they may want to limit or space their families and could benefit from finding a range of methods acceptable.

This will be the first trial evaluating an intervention delivered by mobile phone that is designed to increase the acceptability of effective contraception in Palestine [57]. The results of the study will contribute to the growing body of research on the utility of mobile phones as an intervention-delivery mechanism and contribute to the evidence base for contraceptive interventions for young women in Palestine.

## Methods

### Study design

This study is a parallel-group, individually randomised superiority trial with a 1:1 allocation ratio evaluating the effect of a contraceptive intervention delivered by mobile phone text messaging compared with control text messages about trial participation. The objective of this research is to establish the effect of the intervention on young women’s attitudes towards effective contraception in Palestine.

### Eligibility criteria

Women aged 18–24 years, who do not report using effective contraception, own a personal mobile phone, live in the West Bank, can provide informed consent and can read Arabic will be eligible to take part. The lower age limit of 18 years was chosen because it is the age in Palestine where people are able to provide independent informed consent to take part in research. The upper age limit of 24 years was chosen because this most closely matched the target group ‘young people’ [64] which was identified by the funder. Participants must also be willing to receive messages about contraception on their mobile phone.

### Recruitment

The trial will be promoted through PFPPA’s service-delivery points through outreach sites, the PFPPA website, the distribution of trial promotional material via flyers and social media sites. PFPPA service-delivery points provide: contraceptive methods; counselling for women in psychological, legal and social matters; laboratory tests for both men and women; maternal, antenatal and post-natal care and infertility services [65]. The promotional material includes brief information about the trial (e.g. who is conducting it, who may be eligible, what participation would involve) with a link to the secure trial database and randomisation system.

To maximize the chance of recruiting to target, LSHTM conducted a pre-trial training in Bethlehem to train local staff on all recruitment procedures. The training included discussions about the practicalities of recruitment with a view to developing the most appropriate strategies.

We will report the number of people assessed for eligibility, excluded before randomisation, the number of participants randomised, allocated to the intervention, completed follow-up and analysed (Fig. 1. Consolidated Standards of Reporting Trials (CONSORT) diagram).

**Fig. 1 Fig1:**
[figure not shown]
Consolidated Standards of Reporting Trials (CONSORT) diagram

### Intervention

The intervention is informed by the Integrated Behavioural Model [66] and consists of short mobile phone text messages providing contraceptive support delivered over 4 months. The intervention messages provide information about contraception, target beliefs identified in the development phase that influence contraceptive use (e.g. misconceptions about the side effects and health risks of contraception, belief that non-hormonal methods are better because they are not harmful to health) and aim to support young women in believing that they can influence their reproductive health. The intervention provides accurate information about contraception and contains the following behaviour change methods, adapted for delivery by mobile phone [67]: belief selection, facilitation, anticipated regret, guided practice, verbal persuasion, tailoring, cultural similarity, arguments, shifting perspective and goal setting.

The messages are tailored according to marital status, resulting in two sets of intervention messages: (1) female-married and (2) female-not married. Most of the messages in the two sets overlap, with minor tailoring so that the messages are relevant to marital status (a proxy for sexual activity). Participants allocated to the intervention group receive zero to three messages per day (113 messages for female-not married and 120 messages for female-married) for 120 days.

The message sets start with 6 days of messages (10 messages for married women and 11 for not-married women) with general information about the study, such as information about what they will receive over the next 120 days, how to stop the messages, who to contact if they change their number, how to keep the messages private and information about who to call if they feel unsafe as a result of someone reading the messages. Included in the intervention messages that the intervention recipients receive are seven control messages about the importance of their participation and reminding them to contact the project coordinator if they change their number. On days 119 and 120, the message sets include four messages that indicate that the messages have ended, provide information on how to complete the follow-up questionnaire, reassurance that the information that they provide is confidential and a final message stating that their participation is helping to determine the best ways to provide reproductive health services in Palestine.

Details regarding the development of the intervention and intervention description will be reported in a forthcoming publication.

### Control

Participants allocated to the control group receive 16 messages over 120 days. The first 4 days include six messages that introduce the study, provide information about what they will receive over the next 120 days, how to stop the messages and who to contact if they change their number (e.g. ‘Thank you for joining. This study is being conducted by Palestinian Family Planning and Protection Association’; ‘Over the next 4 months, we will send you a few messages a month’). They will then receive two messages a month for 3 months – one about the importance of their participation and one reminding them to contact the project coordinator if they change their number (e.g. ‘Your participation in the study is a way to actively be involved in matters that affect your life. Thanks’; ‘If you change your number, please contact X to let us know’). On day 105, participants will receive one message about the importance of their participation (‘Your participation helps in reducing inequalities in reproductive health for youth’). On day 120, they will receive three messages that provide information on how to complete the follow-up questionnaire, reassurance that the information that they provide is confidential and a final message stating that their participation is helping to determine the best ways to provide reproductive health services in Palestine (e.g. ‘It is time to complete the final questionnaire. Research staff will call you in few days or you can complete it here LINK’; ‘You are helping us determine the best ways to provide reproductive health services in Palestine’).

All participants will receive usual care and will be free to seek any other support, whether existing or new.

### Outcomes

#### Primary outcome

The primary outcome is the proportion of participants reporting that at least one method of effective contraception is acceptable at four months post randomisation. The acceptability of each method is binary (acceptable/not acceptable), but is derived from ordinal data from the following stems: Using the [method]… causes infertility, …causes unwanted side effects, …is easy, …is a good way to prevent pregnancy and I would recommend the [method] to a friend. The IUD and implant include an additional stem: The [method] insertion would not be a problem for me. The response options for each scale are: strongly disagree, disagree, not sure, agree, strongly agree and I do not know what the [method] is. A method is acceptable if participants report ‘agree’ or ‘strongly agree’ for all scales except for ‘…causes infertility’ and ‘…causes unwanted side effects’ stems, for which ‘disagree’ or ‘strongly disagree’ denotes acceptability (items 1-27 in Additional file 1 and items 4-30 in Additional file 2).

#### Secondary outcomes

Secondary outcomes are: the proportion reporting current use of effective contraception (use of effective contraception); the proportion reporting that each effective contraceptive method is acceptable (acceptability of individual methods); the proportion reporting use of effective contraception at any time during the four months (discontinuation); the proportion reporting attending a sexual health service during the four months (service uptake); the proportion reporting that they became pregnant and did not want to become pregnant during the study (unintended pregnancy); the proportion reporting having an abortion during the study (induced abortion).

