### Sample size

The trial is powered to detect an increase in acceptability of effective contraception. Four hundred and fifty-four participants will allow for 90% power to detect a 15% absolute increase in acceptability, assuming 50% acceptability in the control group (i.e. 50% in the control vs. 65% in the intervention, corresponding to an odds ratio of 1.86). The sample size was calculated using the statistical software Stata 15.0 (syntax: power twoproportions .50 .65, test(chi2) power(0.9)) [68]. A 50% acceptability baseline is used in the absence of published data on acceptability in this context. If the actual baseline acceptability is higher or lower than 50%, the trial is still sufficiently powered to detect an absolute difference of 15%. For example, if the proportion in the control arm is 75%, there will be 90% power to detect an absolute difference of 12% (corresponding to 87% acceptability in the intervention group and an odds ratio of 2.23). Allowing for 20% loss to follow-up, 570 people will be randomised.

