### Analyses

#### General statistical considerations

The analysis of the data will follow the plan specified below. There will be no interim analyses and, therefore, no stopping rules. All analyses will be according to randomised arm and only participants with complete outcome data will be included in the primary analysis (a complete case analysis). All statistical tests will be two-sided. All effect estimates will be reported with a 95% confidence interval and its associated *p* value. Statistical significance will be considered at the 5% level. Analyses will be conducted using the latest version of Stata.

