##### Analysis of the secondary outcomes

The analysis of the secondary outcomes will be the similar to the analysis of the primary outcome. We will estimate the difference between the groups using logistic regression, report odds ratios with 95% confidence intervals and their *p* values. All regressions will be adjusted for the pre-specified covariates as above (although with the acceptability of individual methods, the outcome at baseline will replace acceptability of effective contraception).

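### The secondary outcome named discontinuation is defined as any use of effective contraception in the four months, which measures uptake in women who report no effective method at entry

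*Protocol article*

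**What the plan says.** In the protocol article, *Secondary outcomes* is a list in which each definition is followed by a short name in brackets. Two entries concern use over time:

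- "the proportion reporting current use of effective contraception (use of effective contraception"
- "the proportion reporting use of effective contraception at any time during the four months (discontinuation"

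The abstract's *Methods* paragraph carries the short name forward as an outcome in its own right: "Secondary outcomes include the use of effective contraception, acceptability of individual methods, discontinuation, service uptake, unintended pregnancy and abortion".

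*Eligibility criteria* limits entry to women "who do not report using effective contraception".

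*Analysis of the secondary outcomes* gives one rule for the set, with no exception for this item: "We will estimate the difference between the groups using logistic regression, report odds ratios with 95% confidence intervals and their *p* values". The models are adjusted for the five covariates listed under *Analysis of the primary outcome*. No section of the article defines discontinuation as having started and then stopped, and none gives a denominator for it.

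**The concern.** The definition and its name describe opposite events. Every participant reports being a non-user at entry, so use at some time in the next four months means she began a method. A woman who begins in the first month and is still using at month 4 meets the definition. She is a success for uptake, yet she is counted under a name that means stopping.

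At stake is the reading of one pre-specified, tested secondary outcome. If the intervention raises uptake, the table row headed discontinuation would show an odds ratio above 1. If the intervention changed stopping but not uptake, that row would show nothing. A reader who has only the short name, as in the abstract, would draw the wrong conclusion either way.

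**Working it through.** **The plan's own figure.** The only computed quantity in the article is the primary sample size: "Four hundred and fifty-four participants will allow for 90% power to detect a 15% absolute increase in acceptability, assuming 50% acceptability in the control group". The two-sided 5% two-proportion formula, without continuity correction, gives

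n per arm = [1.960 × √(2 × 0.575 × 0.425) + 1.282 × √(0.50 × 0.50 + 0.65 × 0.35)]² / 0.15² ≈ 226.2, rounded up to 227, so 454 in all.

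Allowing for 20% loss, 454 / 0.80 = 567.5, or 568, against 570 stated. The figures reproduce, and the present point does not depend on them.

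**Definition against name.** No assumption is needed here.

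1. Entry status: no effective method reported (*Eligibility criteria*).
2. Event as defined: effective method used at some time in the four months (*Secondary outcomes*).
3. From 1 and 2, the event is starting a method after entry.
4. Stopping needs a second condition, no current use at follow-up. The definition does not contain it.

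**What the odds ratio would respond to.** The article gives no rates, so all rates below are assumed, control v intervention. Used-and-stopped is ever-use minus current use, taking every current user to be an ever-user. The odds ratio is OR = [p₁/(1 − p₁)] / [p₀/(1 − p₀)].

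| Case | Ever-use | Current use | OR, outcome as defined | Used and stopped, all women | OR, used and stopped | Stopped, among ever-users |
|---|---|---|---|---|---|---|
| 1 | 10% v 20% | 8% v 16% | 2.25 | 2% v 4% | 2.04 | 20% v 20% |
| 2 | 10% v 20% | 8% v 18% | 2.25 | 2% v 2% | 1.00 | 20% v 10% |
| 3 | 10% v 20% | 5% v 19% | 2.25 | 5% v 1% | 0.19 | 50% v 5% |
| 4 | 10% v 10% | 8% v 4% | 1.00 | 2% v 6% | 3.13 | 20% v 60% |

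The arithmetic:

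- Outcome as defined, cases 1 to 3: (0.20/0.80)/(0.10/0.90) = 2.25.
- Used and stopped, case 1: (0.04/0.96)/(0.02/0.98) = 2.04.
- Used and stopped, case 3: (0.01/0.99)/(0.05/0.95) = 0.19.
- Used and stopped, case 4: (0.06/0.94)/(0.02/0.98) = 3.13.

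The outcome as defined follows ever-use alone. It is 2.25 in cases 1 to 3, although stopping differs in each, and 1.00 in case 4, where stopping triples.

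**What a used-and-stopped outcome would offer.** Case 1 has 80% of starters continuing in both arms, so there is no difference in continuation. The all-women odds ratio is still 2.04, because more starters means more women who can stop. With 227 analysed per arm, events are 227 × 0.02 = 4.5 and 227 × 0.04 = 9.1, about 14 in all. The planned model has six coefficients besides the intercept (arm plus five covariates), so 14/6 gives little more than two events per coefficient.

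**The case against.** The strongest reply is that the event is written out in full beside its short name. The tested quantity is thus pre-specified, and a results table that carries the full definition would mislead nobody. The authors may also have meant the two use items to be read as a pair. These points reduce the severity but do not remove the inconsistency. The abstract already uses the bare name, and the article nowhere says that the two proportions are to be compared.

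A reader might infer that discontinuation could not be estimated at all under this plan. The article does not support that. Current use and any use are both secondary outcomes by arm, and their difference recovers the share of women who used and stopped, provided both items are put to everyone. The questionnaire is in Additional file 2, which is not shown, so the routing of the items is unknown. For the same reason, it cannot be taken for granted that a derived variable needs no new data.

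A reader might also infer that testing used-and-stopped among all followed-up women would cure the problem. It would not. In case 1 above it leaves an odds ratio of 2.04 in place of 2.25 when continuation is identical, and it rests on very few events. The comparison among ever-users shows no difference in that case, but its denominator is formed after randomisation and is not protected by it.

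Finally, the article assigns no good or bad direction to this outcome, so calling a rise a harm would be the reader's own gloss.

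A fuller analysis plan might exist, but this is not an omission that an article may leave to it. The article states a definition and a name, and they cannot both be right.

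**Conclusion.** The outcome is wrong as written and should be fixed. The contradiction between name and definition follows from *Secondary outcomes* and *Eligibility criteria* alone. Its effect is that initiation would be reported, with an odds ratio and p value, under the name of stopping. The 2.25 is an illustration under assumed ever-use of 10% v 20%, not a prediction.

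The point does not reach the main result. It concerns one of several secondary outcomes. The primary outcome, its analysis and the sample size of 454 analysed and 570 randomised stand as they are.

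**What to change.** 1. Rename the stated measure *any use of effective contraception during the 4 months*, in *Secondary outcomes* and in the abstract, and keep its planned adjusted logistic regression.
2. If discontinuation is wanted as well, define it as any use during the 4 months with no current use at follow-up. First confirm that the follow-up questionnaire asks both items of all participants.
3. Report discontinuation by arm mainly descriptively, both as a share of all followed-up women and as a share of ever-users.
4. State three limits beside it: the all-women share rises with uptake even when continuation is equal, the ever-user denominator is formed after randomisation, and events may be too few for the five-covariate model.

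The renaming costs one change of wording in two places. The optional outcome costs a short definition and one derived variable. If the questionnaire does not ask both items of everyone, the derivation may not be possible from the data collected, and the renaming alone should then be made.
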